### Statistical Analysis

Between-group differences in primary and secondary outcomes will be analyzed using intention-to-treat and per-protocol analyses. Continuous outcomes will be analyzed using standard *t* tests (2-tailed and unpaired) and multivariable linear and mixed regression models to adjust for potential differences between groups occurring by chance. Categorical outcomes will be analyzed with chi-square tests and multivariate logistic regression analyses. When analyzing longitudinal data, multivariate regressions with clustered standard errors, multilevel models, or generalized estimating equations may be used to account for the correlation between repeated measurements.

Potential interaction effects between the interventions and relevant covariates such as age at diagnosis, disease characteristics (triple negative, HER2+, or DCIS), and primary treatment will also be explored, either by stratification or by estimating multivariate models including interaction effects.

Missing data will be handled using multiple imputation techniques, primarily if the proportion of participants with missing information exceeds 15%. A detailed description of statistical analysis will be developed. All statistical analyses will be performed using STATA statistical software version 15 or later (StataCorp LLC).

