#### Coping After Breast Cancer Questionnaire

Participants receive the baseline CABC survey at approximately 7 months after diagnosis and the follow-up CABC surveys 13, 24, and 35 months after diagnosis (Figure 1). The follow-up surveys were sent about 1 month after the CRN PROMs surveys, in order for participants not to confuse the 2 data collections.

The Cohen 10-item Perceived Stress Scale [76] in the CABC survey will be used to assess the primary outcome: 6-month change in perceived stress (from 7 to 13 months following diagnosis) between each of the intervention groups and TAU (Table 1).

The following secondary outcomes are also obtained from the CABC survey: distress ranging from sadness and worry to anxiety and depression, as measured by the Brief Version of the Patient Health Questionnaire for Depression and Anxiety [80]. (Health-related) quality of life is measured by the RAND Corporation 36-Item Short Form Health Survey (RAND-36). RAND-36 assesses 8 health concepts: physical functioning, role limitations caused by physical health problems, role limitations caused by emotional problems, social functioning, emotional well-being, energy/fatigue, pain, and general health perceptions [11]. Mindfulness is assessed using the 15 items from Baer’s 5 Facet Mindfulness Questionnaire [49]. Sleep (duration and quality) is measured by items from the Norwegian Shift Work, Sleep and Health survey [81]. Coping, defined as 3 dimensions of response outcome expectancies related to an individual’s ability to handle stressors and challenges in everyday life related to coping, hopelessness, and helplessness, is measured by the Theoretically Originated Measure of the Cognitive Activation Theory of Stress [77].

As there is no CRN PROMs survey 24 months after diagnosis, the work-related outcomes are included in the CABC survey after 24 months, whereas Chalder’s Fatigue Scale is included at baseline and at month 24 (Table 1).

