### Sample Size Calculations

Power calculation in the CABC trial was conducted on the primary outcome (ie, 6-month between-group difference in perceived stress) using independent sample *t* tests. The α level was adjusted for multiple comparisons (comparing 2 intervention groups with 1 control group for each outcome) by setting the significance level to 2.5%. Estimates of effect sizes and SDs were retrieved from previous StressProffen interventions on multiple groups of patients with cancer, which found a mean difference in perceived stress of 2.8 and SDs of 6.6 and 8.3 in the case and control groups, respectively [70]. As the CABC trial includes a more homogenous population (only female patients with breast cancer), the effect size was set to 3 and the SD to 6.

With an estimated 80% power to detect a difference between 1 of the intervention groups and the control group, a sample size of 235 participants is needed. With an assumed completion rate of 70%, a total of 335 participants will need to be enrolled, 70 in each group.

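### The trial is powered on an unadjusted t test, and the article does not say which of three listed analyses decides the primary hypothesis or name baseline PSS-10 as a covariate, which gives up precision that is free to recover

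*Protocol article*

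**What the plan says.** - **Primary outcome** (Protocol article, Coping After Breast Cancer Questionnaire): "6-month change in perceived stress (from 7 to 13 months following diagnosis) between each of the intervention groups and TAU".
- **Analysis of continuous outcomes** (Statistical Analysis): standard *t* "tests (2-tailed and unpaired) and multivariable linear and mixed regression models to adjust for potential differences between groups occurring by chance". The same section calls for both intention-to-treat and per-protocol analyses. It offers several repeated-measures methods as possibilities and says that a fuller description of the analysis is still to be written.
- **Sample size** (Sample Size Calculations): the calculation addresses the "6-month between-group difference in perceived stress) using independent sample" *t* tests. Two comparisons with control are allowed for "by setting the significance level to 2.5" percent. On the planning values, "the effect size was set to 3 and the SD to 6". The result is given as "With an estimated 80% power to detect a difference between 1 of the intervention groups and the control group, a sample size of 235" participants, raised to 335 for 70% completion.
- **Missing data** (Statistical Analysis): "Missing data will be handled using multiple imputation techniques, primarily if the proportion of participants with missing information exceeds 15" percent.
- **Availability of baseline** (Randomization; Table 1): a woman is allocated only after submitting the baseline survey, and that survey contains the PSS-10.

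**The concern.** Three kinds of analysis are listed for one primary outcome: a *t* test, a linear model and a mixed model. Nothing ranks them. The alpha adjustment covers only the two comparisons with control, not a choice among methods. If the methods disagree, the article does not say which one settles the hypothesis.

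The reason given for adjustment is also the weaker one. In a randomised trial the main case for adjusting is that a covariate predicts the outcome and so reduces residual variance, whether or not the arms happen to differ. The baseline value of the outcome is usually the strongest such covariate. Here it should be on file for every randomised woman.

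What is at stake is precision and a clear decision rule. The Results section reports signs of lower completion than expected, so precision is worth having. A secondary matter is that the use of imputation is loosely tied to an observed proportion of missing data.

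**Working it through.** **Inputs from the article.** Difference 3; SD 6; significance level 0.025 per comparison; power 80%; two-sided, because the tests are "tests (2-tailed and unpaired"); allocation 1:1:1; completion 70%. The article does not say whether 6 is the SD of the score or of the change. It also gives no correlation r between baseline and 13 months, so r is assumed over 0.3 to 0.7.

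**Step 1: reproduce the plan's figure.** Per arm, n = 2(z₀.₉₈₇₅ + z₀.₈₀)² / (3/6)² = 2(2.2414 + 0.8416)² / 0.25 = 76.04, so 77 per arm and 231 in all. The exact *t* calculation gives 77.3, so 78 per arm and 234 in all, against the stated 235. Then 234/0.70 = 334.3, which rounds up to the stated 335. The plan's figures therefore follow from an unadjusted two-sided *t* test, with no credit for baseline.

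**Step 2: compare variances.** Let σ be the SD of the score, taken as equal at both times.

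- Final score alone: σ²
- Change score: 2σ²(1 − r)
- Baseline-adjusted (ANCOVA): σ²(1 − r²)

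ANCOVA over change = (1 − r²) / [2(1 − r)] = (1 + r)/2. At r = 0.5, 0.6 and 0.7 this is 0.75, 0.80 and 0.85, a saving of 25%, 20% and 15%. The ratio is below 1 for every r below 1.

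**Step 3: power at 78 per arm.** Power = Φ(3 / (s√(2/78)) − 2.2414), where s is the SD that applies to the analysis. With s = 6 this is Φ(3.122 − 2.241) = 81%; the exact *t* value is 80.4%.

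*If 6 is the SD of change*, the *t* test on change has s = 6 and ANCOVA has s = 6√((1+r)/2):

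| r | s, ANCOVA | Power, ANCOVA | Power, *t* test on change |
|---|---|---|---|
| 0.3 | 4.84 | 95% | 81% |
| 0.4 | 5.02 | 93% | 81% |
| 0.5 | 5.20 | 91% | 81% |
| 0.6 | 5.37 | 89% | 81% |
| 0.7 | 5.53 | 87% | 81% |

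*If 6 is the SD of the score*, the *t* test on change has s = 6√(2(1−r)) and ANCOVA has s = 6√(1−r²):

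| r | s, change | Power, *t* test on change | s, ANCOVA | Power, ANCOVA |
|---|---|---|---|---|
| 0.3 | 7.10 | 65% | 5.72 | 85% |
| 0.4 | 6.57 | 73% | 5.50 | 88% |
| 0.5 | 6.00 | 81% | 5.20 | 91% |
| 0.6 | 5.37 | 89% | 4.80 | 95% |
| 0.7 | 4.65 | 96% | 4.28 | 98% |

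On this second reading the change-score *t* test reaches its planned power only if r is about 0.5 or more. Below that, subtracting baseline adds more noise than it removes.

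**Step 4: the missing-data threshold.** Planned completion of 70% means 30% loss, twice the 15% threshold, and the Results section reports signs that completion was lower still. If completion here means return of the 13-month survey, the condition for imputation is expected to be met for the primary outcome.

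**The case against.** The strongest reply is that the article already lists regression and mixed models, that a detailed analysis description is announced, and that the *t* test on change is valid under randomisation. Step 1 also shows that the sample size is correctly derived for that test. The target was later raised to 430, about 100 in each group. With 100 analysed per arm and an SD of 6 for the quantity tested, the unadjusted test would itself have about 90% power. All of this stands. It lowers the weight of the point but does not answer it: the analysis is still not named, and baseline adjustment would still add precision at no cost.

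A reader might infer more than the article supports:

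- **That the primary comparison is fixed as an unadjusted *t* test.** The text joins *t* tests and regression. Only the power calculation rests on the *t* test.
- **That the baseline score is thrown away.** A change score subtracts it. The fair criticism is inefficient use.
- **That only completers are analysed.** The article specifies intention-to-treat analysis as well as per-protocol, and multiple imputation.
- **That covariates will be picked after looking at the arms.** The article gives a purpose for adjustment, not a selection rule. Its wording is compatible with a list fixed in advance.
- **That imputation is barred below 15% missing, so unequal loss between arms could go unaddressed.** The article says the threshold applies primarily, not exclusively, and does not say how the proportion is computed. On the trial's own figures it should be exceeded.

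The full covariate list, the imputation model and the sensitivity analyses properly belong in the announced analysis description. Their absence here is no fault.

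**Conclusion.** The point holds as a matter of efficiency and clarity, not of validity. The article powers the trial on an unadjusted *t* test, lists three kinds of analysis without saying which decides, and does not name the most obvious covariate.

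Baseline adjustment cuts variance by 15 to 25% relative to the change-score *t* test for r between 0.7 and 0.5. If 6 is the SD of change, power at 78 per arm rises from about 80% to between 87% and 91% over that range. If 6 is the SD of the score, the change-score *t* test falls short of 80% once r is under about 0.5, while ANCOVA stays at 85% or above for every r examined.

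These figures rest on an assumed r, on equal SDs at the two times, and on an SD whose meaning the article leaves open. They do not show that the trial is too small. The missing-data threshold is a minor addition and is unlikely to alter the primary analysis. The change is worth making, but it is not a condition for the trial to be interpretable.

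**What to change.** Name one primary analysis in the announced analysis description: a linear or linear mixed model of the 13-month PSS-10 on arm, adjusted for baseline PSS-10, in all randomised participants. Fix any further covariates in advance. Justify adjustment by prognostic value rather than by chance imbalance. Keep the *t* test as supportive. State whether the planning SD of 6 refers to the score or to the change.

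As a secondary change, use one missing-data method (likelihood-based or multiple imputation) whatever proportion is missing, and drop the 15% condition.

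The cost is a few sentences and minor programming. Baseline PSS-10 is already collected before allocation, and neither the sample size nor the data collection needs to change.

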## Results

During inclusion there were signs that the completion rate among participants was lower than expected. By contrast, during the pandemic, a higher than expected percentage of newly diagnosed patients with breast cancer were digitally active (88% in 2022), which resulted in an increase in the percentage of eligible patients with breast cancer that were invited to the CRN PROMs survey in 2022. This provided an opportunity to account for the lower completion rate by recruiting more participants. The target number was therefore increased from 335 to 430 participants (about 100 in each group; enrollment end date May 31, 2023). As of April 14, the total number recruited is 428.

The project has received funding from the Norwegian Breast Cancer Society’s “Pink Ribbon” charity funding (principal investigator: GU).

## Discussion

### Impact of Stress Management

Psychosocial and physical long-term complaints after breast cancer treatment remain a major public health challenge with substantial social and personal costs [9]. Psychosocial stress can be associated with inflammation, tumor progression, and disease prognosis [55,91,92], as well as increased risk and prognosis of other chronic diseases [93,94]. Stress management interventions have been effective in reducing stress and other long-term complaints following a cancer diagnosis [64]. Cancer survivors using the original StressProffen intervention (ie, with a combination of CBT and MBI) over a 12-month study period reported significantly greater reduction in perceived stress, depression, and anxiety compared with controls (ie, TAU). The intervention also showed significantly improved health-related quality of life for cancer survivors receiving StressProffen compared with controls [71].

The CABC trial will study similar outcomes as in the original StressProffen intervention, but solely in breast cancer survivors and with additional long-term follow-up. If any or both of the current interventions have effects that are superior to findings from the TAU control group, implementation of the convenient eHealth intervention StressProffen should be considered in clinical practice, perhaps as a future extension to precision oncology care [55].

The original StressProffen program (ie, the app) targeting cancer survivors is in the process of being made commercially available in English and Norwegian versions, whereas the StressProffen-CBI and MBI versions are only available for study participants. Future distribution will depend on study findings.

### Strengths

The CABC trial is, to our knowledge, currently the largest psychosocial eHealth intervention (RCT) in patients with breast cancer. The trial has a long-term follow-up with an assessment of intervention effects 1, 2, and 3 years after a breast cancer diagnosis, corresponding to up to 29 months after baseline. Furthermore, study participants can be prospectively followed up with respect to comorbidity, relapse and new cancers, and mortality until the end of the study (ie, currently, December 31, 2035) through linkage with national health registries using personal identification numbers (mandatory for all Norwegians). The feasibility of the StressProffen app was assessed initially by [name] and colleagues [71] and the CABC trial has further extended the StressProffen research line through developing the StressProffen-CBI and StressProffen-MBI interventions, pilot tested these, and implemented necessary adjustments. Another strength of the trial is the ongoing systematic collection of CRN PROMs survey data. This enables us to compare study participants with all CRN PROMs survey data.

Development of the 2 interventions strived to balance design and content presentation to enhance the chance of any effect differences arising due to theoretical content (ie, CBI/MBI). However, due to statistical power limitations, direct comparisons of the 2 interventions will solely be conducted on an exploratory basis. The flexibility of the intervention can be beneficial for patients with cancer undergoing treatment while coping with everyday activities [64]. Given the high percentage of the population that has access to digital platforms within Norway [68], the study has a unique possibility to recruit participants across different socioeconomic statuses and geographical locations. Digital intervention delivery also demands less resources than face-to-face interventions [56]. Thus, if found to be effective, the StressProffen eHealth intervention may have a better chance of being integrated as part of clinical practice than costly face-to-face interventions.

### Limitations

The CABC trial has some limitations. First, outcome measures are primarily self-reported. Second, data related to outcomes prior to breast cancer diagnosis are not available. Third, the study only includes a subsample of patients with breast cancer with either noninvasive disease (DCIS) or severe (triple-negative or HER2 positive) breast cancer. Participants are therefore likely to be a heterogenous group of patients with breast cancer with varying treatment according to stage and subtype (eg, in addition to surgery, patients with DCIS may only receive radiation therapy, whereas patients with triple-negative or HER2-positive cancer are advised chemotherapy for several months) [95]. Selection bias may be present as participation depends on the use or access to the digital mailbox and willingness to participate in the CRN PROMs survey (ie, about 50%) [68]. These factors could also limit the generalizability of the study results. However, an eHealth intervention requires the use of digital resources and access to digital tools as requirements.

### Conclusions

The CABC trial is possibly the largest ongoing psychosocial eHealth RCT in patients with breast cancer. If 1 or both interventions prove to be effective in reducing stress and improving psychosocial and physical complains, the StressProffen eHealth interventions could be beneficial, inexpensive, and easily implementable tools for breast cancer survivors when coping with late effects after cancer and cancer treatments.

## Appendix

Multimedia Appendix 1 Standard Protocol Items: Recommendations for Interventional Trials (SPIRIT) checklist.

## Abbreviations

CABC: Coping After Breast Cancer
CBI: cognitive behavioral intervention
CBT: cognitive behavioral therapy
CRN: Cancer Registry of Norway
DCIS: ductal carcinoma in situ
EORTC QLQ: European Organization of Research and Treatment of Cancer-Core Quality of Life Questionnaire
EORTC QLQ-BR23: European Organization of Research and Treatment of Cancer-Core Quality of Life (Breast Cancer–Specific Module) Questionnaire
EORTC QLQ-C30: European Organization of Research and Treatment of Cancer-Core Quality of Life Questionnaire
ER: estrogen receptor
HER2: human epidermal growth factor receptor 2
ICD-10: International Classification of Diseases, 10th revision
MBI: mindfulness-based intervention
PROM: patient-reported outcome measure
RAND-36: RAND Corporation 36-Item Short Form Health Survey
RCT: randomized controlled trial
SPIRIT: Standard Protocol Items: Recommendations for Interventional Trials
TAU: treatment as usual
